## Abstract

**Background:**

Mobile phone short messaging services (SMS) have been investigated in health information reporting, provider performance, drug and diagnostic stock management and patient adherence to treatment for chronic diseases. However, their potential role in improving patients’ adherence to malaria treatment and day 3 post treatment reviews remains unclear.

**Methods/Design:**

A “proof of concept” open label randomised controlled trial will be conducted at four sites in Western Kenya. Principal research questions are: 1) Can mobile phone SMS reminders improve patient adherence to malaria treatment? 2) Can mobile phone SMS reminders improve day 3 post treatment reviews? Eligible caregivers (n=1000 per arm) of children under five years old with uncomplicated malaria will be randomly assigned (one to one) to: a) the current standard of care (provider counselling and health education); and b) the current standard of care plus SMS reminders. Within each arm, caregivers will be further randomized to three different categories. In categories 1 and 2, 300 caregivers per arm per category will be visited at home on day 1 and 2 of follow up respectively, to measure appropriate timing and adherence of the second Artemether-Lumefantrine (AL) dose and doses 3 and 4. Further, caregivers in categories 1 and 2 will be required to come to the health facility for the day 3 post treatment reviews. Finally, in category 3, 400 caregivers per arm will be visited at home on day 3 to measure adherence for the full AL course. Each category will be visited at home only once to avoid biases in the measures of adherence as a result of home consultations. Primary outcomes will be adherence to the full AL course (category 3), as well as, the proportion of patients reporting back for day 3 post treatment reviews (categories 1 and 2). The primary analysis will be intention-to-treat. Costs of the intervention will be measured over the period of the intervention, and a cost-effectiveness ratio will be estimated.

**Discussion:**

If successful, evidence from this trial could improve malaria treatment adherence and offer pragmatic approaches for antimalarial drug resistance surveillance and risk mitigation in Africa.

**Current Controlled Trials:**

ISRCTN39512726

## Background

Artemisinin resistant *Plasmodium falciparum* malaria has emerged in south East Asia (SEA), with possible foci in Western Cambodia, Western Thailand, Myanmar and possibly beyond [1–3]. This poses a major global public health threat, with the greatest potential effects in sub-Saharan Africa where the malaria burden is greatest and systems for resistance surveillance and risk mitigation are weakest. A public health disaster is imminent unless mitigation, early warning and early detection measures are urgently set up in Africa. The main phenotypic trait associated with artemisinin resistance is a substantial delay in parasite clearance, so far observed in SEA but not yet unequivocally confirmed in Africa [4]. Despite calls for the reactivation of drug resistance surveillance networks in Africa [5,6]; coordinated and proactive efforts to address the threat of artemisinin resistance are limited. A recent case report of severe malaria that manifested after 4 days in a patient who returned to Vietnam from Angola, where he had lived for 3 years, and was not responsive to intravenous artesunate plus clindamycin or oral dihydroartemisinin-piperaquine needs further investigation [7].

Early detection of emerging Artemisinin resistance in Africa is likely to require wide coverage surveillance, beyond the traditional sentinel surveillance. Consequently, robust collection of the proportion of patients who remain parasite positive at day, if feasible, could offer highly sensitive and pragmatic metrics for tracking emerging Artemisinin resistance [8,9]. Such metrics could provide early evidence of a congruence of factors in “hotspots”, which could be designated, drug resistance surveillance sites; be targeted for investigative clinical trials with 6-8 hourly parasite density sampling; or could be targeted for molecular surveillance, as and when molecular markers for artemisinin resistance become well established and validated [6,10]. However, in Africa, routinely conducting day 3 post treatment reviews to estimate the proportion of patients with persistent patent parasitaemia after 72 hours is often not carried out. Consequently, innovative ways of promoting this practice are urgently needed.

Poor patient adherence to treatment and drug misuse are among some of the drivers of resistance [11]. Poor adherence is likely to decrease cure rates and to favour the emergence of resistance because parasites are exposed to sub therapeutic drug concentrations. Evidence from systematic reviews suggests variable outcomes of adherence to malaria treatment, ranging from sub-optimal (less than 50%) to very high (90-100%) [12–15]. The varying adherence estimates are probably due to factors related to patient characteristics and the nature of their consultation with the provider or methodological variations such as the interaction between the research team and patients before and during treatment. A recent systematic review has suggested that future studies of adherence to malaria treatment could benefit from an awareness of the impact of study procedures on adherence outcomes, and has proposed the identification of improved measurement methods less dependent on self-reporting [13]. Presently, the most widely used methods for adherence measurement are conducted after completion of a full dose of Artemether-Lumefanthrine (AL). However, these methods rarely consider the timing of dosing and depend on self-reporting which has inherent recall bias resulting in unreliable measurements of adherence to AL dosing schedules. AL is presently the most widely used artemisinin combination therapy (ACT) in rural Africa, but AL has a relatively complex dosing scheme, requiring twice a day drug administration with the second dose spaced 8 hours after the first dose. From literature review, only one study has attempted to measure the timing of individual AL doses [16]. There is therefore a need to investigate better approaches for measuring and improving adherence to malaria treatment and this research aims to provide the much needed evidence base.

Mobile phone short messaging services (SMS) could improve the delivery of health services in Africa and their role has been investigated in health information reporting, provider performance, drug and diagnostic stock management and patient adherence to treatment for chronic diseases such as HIV/AIDs [17–25]. However, the efficacy of SMS reminders in improving patients’ adherence and day 3 post treatment reviews for acute diseases such as malaria has not been widely investigated. At the time of writing this protocol, no peer reviewed studies had been published that have investigated the impact of SMS reminders sent to caregiver’s mobile phones on malaria treatment adherence and day 3 post treatment reviews. In Kenya, the coverage of mobile phones has increased in the recent past and many districts have universal mobile network coverage [26,27]. The efficacy of mobile phone SMS reminders in improving malaria treatment adherence and day 3 post treatment reviews in children with uncomplicated malaria in Kenya will be investigated in an endeavour to improve malaria treatment adherence as well as investigate novel approaches for early warning and early detection of emerging Artemisinin resistance in Africa.

## Methods/Design

### Overall study design

The research is being conducted in three phases. Phase I, was an assessment of the feasibility, patterns of use and acceptability of using mobile phone SMS reminders for malaria treatment adherence and day 3 post treatment review. Thereafter, through an iterative process involving multi-disciplinary teams, the research team developed; pilot tested and finalized the intervention. Phase II, which commenced in June 2014, is a randomized controlled trial (RCT) to assess the efficacy of the SMS intervention. Finally, in phase III, qualitative research to describe the factors contributing to the success or failure of the intervention and cost-effectiveness analysis of the intervention with respect to the primary outcomes–adherence and day 3 post treatment reviews will be undertaken.

### Trial sites

The research is being conducted at four sites in Kenya. Two sites (Bondo and Got Agulu hospitals) are located in Bondo district, while the other two sites (Ndori health centre and Madiany hospital) are located in Rarieda district (Figure 1). All trial sites are government owned public health facilities. Bondo District hospital is a referral facility and the only one located in an urban area. According to the 2009 census, Bondo and Rarieda districts have a combined population of 29,080 with a density of 997 persons per km^2^. The population is predominantly of Luo ethnicity and earns its living through subsistence farming and fishing. The area is largely rural with urban settlement limited to one town, Bondo. These two districts have high malaria transmission (parasite prevalence among children 2-10 years above 40%) [28]. More detailed descriptions of the study sites are published elsewhere [29].

### Description of the study phases

**Phase 1–Development of the intervention:** The intervention is based on a one-way automated distribution of SMS reminders for AL adherence and day 3 post-treatment reviews sent to caregivers’ personal mobile phones or phones that they have access to in the household. The primary objective of phase 1 of the research was the development, refinement and finalisation of the intervention. The detailed descriptions of the intervention development process and the qualitative research conducted will be published elsewhere [[name] et al., manuscript in preparation]. In brief the intervention development process was conducted through a six step process, namely:

**Step 1:** Despite the high coverage of the network signal and mobile phone access from nationally representative surveys [26,27] facility-based exit surveys were conducted at the study sites to validate these national statistics and gather additional information from caregivers pertinent to the development and delivery of the SMS intervention. The details of the feasibility assessment have been published elsewhere [29]. Briefly, out of 400 interviewed caregivers, nearly all (99.8%) reported access to a mobile signal at home. Ninety three percent (93%) had access to a mobile phone within their household while 73.8% possessed a personal phone. Among caregivers with mobile phone access, 93.6% used the phone to receive text-messages. The willingness to receive text-message reminders was nearly universal (99.7%) with 41.7% of caregivers preferring texts in English, 32.3% in Kiswahili and 26.1% in Dholuo language [29].

**Step 2:** In this step, the various modalities of the intervention delivery were considered, including: the number, content, length, frequency and languages to be used for text messages. An intervention development workshop was conducted, involving clinicians and caregivers from the areas neighbouring the study sites, malaria epidemiologists, social scientists, mobile health programmers, and members of the district health management teams.

**Step 3:** The understanding of the messages developed was pre-tested using focus group discussions (FGDs). FGDs were conducted among caregivers from the study sites to ensure that the messages were clearly understood by the target group. Twenty caregivers of sick children from the study health facilities were invited to participate in the FGDs during which they received SMS text messages in Dholuo, English or Kiswahili based on their language preference. Members of the groups discussed the meaning and understanding of the messages. Following the testing, the messages were amended as required.

**Step 4:** A computerized SMS distribution system was developed by mobile phone programmers to ensure the automated SMS distribution to individual recipients upon their registration into the system. The system is a web-based application platform optimized for data collection and reporting. It is composed of: (1) an SMS data collection tool which uses a built-in SMS gateway to receive and send structured SMS messages according to the language option preferred by the caregiver, which are then stored in a local database and (2) an analytics tool that enables visualization and analysis of data sent via SMS to help real time tracking of the operational progress of the trial. Upon registration, the system creates a schedule of reminder messages to be sent at specific timings and generates log reports of all messages scheduled and those already sent.

**Step 5:** Pilot testing of the automated distribution system and the selected messages was conducted, during a complete delivery of the intervention to 40 healthy recipients including all study investigators, and 20 malaria caregivers at health facilities not involved in the RCT. All malaria caregivers receiving the messages were visited by a social scientist to solicit their views and experiences of the pilot intervention.

**Step 6:** Finally, based on the results of the pilot test, the content and modalities of the text-message distribution was finalized before being deployed in the RCT. The English version of the text-messaging content with timing of SMS distribution is presented in Table 1.

### Phase 2 – The randomized controlled trial

**Trial design:** Caregivers of eligible children with uncomplicated malaria will be randomly assigned (one to one) to two different arms: 1) the current standard of care based on provider counselling and health education alone, and 2) the current standard of care plus SMS reminders. Within each arm participants will be further randomly assigned to 3 different categories for the measurement of adherence to the different doses of AL. In the first category, 600 caregivers (300 per arm) will be visited at home on day 1 of follow up to measure adherence and timing of the second AL dose; in the second category, another 600 caregivers (300 per arm) will be visited at home on day 2 to measure adherence and timing of AL doses, 3 and 4, while, in the third category, a final 800 caregivers (400 per arm) will be reviewed at home on day 3 after they have completed the full treatment course to measure adherence for the full course of AL. All caregivers in each category will be visited at home only once to avoid biases in the subsequent measures of adherence as a result of the consultations at home. Caregivers in category 1 and 2 will be required to come to the health facility for the day 3 post treatment reviews, while those in category 3 will be visited at home on day 3.

AL will be administered according to weight bands: 5-14 kg, 1 tablet twice a day for three days, 15-24 kg, 2 tablets twice a day for three days and will be directly observed for the first dose, with the remaining 5 doses being provided for administration at home. All caregivers will receive standard instructions about how to administer AL at home and when to return to the facility for scheduled visits or immediately if unwell. At first dose administration, the telephone numbers of all eligible caregivers will be registered into the automated system by the randomizing nurse who will also observe directly supervised therapy of the first dose. The registration will record the time when the first dose is administered. A procedure for guiding the correct registration of the random number that will act as a unique identifier has been put in place (Figure 2).

In the intervention arm the registration generates a programme that automates SMS reminders from a central server, timed to eight hours after the first AL dose for the second dose and then every morning and evening (8 am and 8 pm) until the full AL course is completed. To limit the number of follow up SMS messages being received at very late hours of the night, patient recruitment will be stopped by 2 pm. Caregivers in category 1 and 2 in the intervention arm will in addition to the SMS dose reminders also receive an SMS reminder for the day 3 post treatment reviews at the health facility the evening before and on the morning of the appointment. Since caregivers in category 3 (intervention and control) will be reviewed at home on day, they will not receive SMS reminders for the day 3 post treatment reviews. Weekly SMS reminders (day 7, 14 and 21) prompting caregivers to visit the health facility if their child is unwell will be sent to participants in the intervention arm. If such reminders result in a visit to the health facility, such a visit will be considered an un-scheduled visit. Finally, participants in the intervention arm will be sent final SMS reminders on the evening before and on the morning of the day 28 post treatment review appointment. Patients who do not return for post treatment review (intervention and control arms) will not be actively followed up.

### Allocation of participants to trial groups

In order to ensure concealment of the intervention allocation to the trial staff, the randomization to the two study arms and subsequently to the 3 adherence measurement categories per arm was generated by an offsite statistician. Intervention allocation is concealed from the study staff reviewing the patients for treatment outcomes until evaluation is completed. However, such concealment could not be implemented for those conducting the home visits since they also collect data on SMS exposure, but we believe this lack of concealment will not affect the adherence outcome because the home visit will be conducted after the AL dose has been administered. Since caregivers will be visited at home only once, we will not measure adherence of the subsequent doses of AL in category 1 and 2. We designed the study to measure adherence to the full course of AL only in category 3 when all doses should have been completed to enable comparison with previous studies.

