### Quality control and limitation of bias

The major source of bias in adherence studies is reliance on participant recall and the possibility of false reporting. We have adopted an innovative approach of measuring adherence on different days during the dosing period, which is likely to reduce recall bias for the doses on days 1 and 2 in category 1 and 2 but not in category 3. The second primary outcome measure (day 3 post treatment review) requires objective assessment and we do not anticipate any biases in its measurement. The trial will be conducted under strict adherence to good clinical practice (GCP) standards.

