### Primary outcomes

The first primary outcome will be adherence to a complete AL course (doses 2-6) measured in category 3 only and defined as: a) adherent, if they present with empty blister packs and report taking the medications as recommended (± 1 hour for dose 2 and ± 2 hours for doses 3-6); b) probably adherent if they do not present blister packs but report taking the medications as recommended, c) probably non adherent if they do not present blister packs and do not report taking the medications as recommended, and d) non adherent if they present blister packs with at least one tablet not used. The second primary outcome will be the proportion of patients reporting to the health facility for the day 3 post treatment review for the evaluation of clinical and parasitological cure at day 3 (only category 1 and 2).

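### That the home visit follows dosing does not protect how reported adherence is recorded by visitors who know the arm; differential recording stays possible, with unknown direction and size

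*Protocol article*

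**What the plan says.** The Abstract (Methods/Design) calls the trial open label: "A “proof of concept” open label randomised controlled trial will be conducted at four sites in Western Kenya". Under Allocation of participants to trial groups, masking is kept for one group of staff: "Intervention allocation is concealed from the study staff reviewing the patients for treatment outcomes until evaluation is completed". Home visitors are excepted: "such concealment could not be implemented for those conducting the home visits since they also collect data on SMS exposure". The article then gives its reason for expecting no harm, introduced as a belief: "this lack of concealment will not affect the adherence outcome because the home visit will be conducted after the AL dose has been administered".

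The trial design paragraph of Phase 2 adds that "All caregivers in each category will be visited at home only once", so adherence and SMS exposure are collected at the same visit.

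Under Primary outcomes, measured in category 3, a child is "adherent, if they present with empty blister packs and report taking the medications as recommended", with windows of ±1 hour for dose 2 and ±2 hours for doses 3-6. A child is "probably adherent if they do not present blister packs but report taking the medications as recommended". The probably non-adherent class also has no pack. The non-adherent class is set by at least one tablet left in a presented pack. Caregiver report and pill count are the two sources named for measuring adherence.

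Under Quality control and limitation of bias: "The major source of bias in adherence studies is reliance on participant recall and the possibility of false reporting". The same section says the staggered visits are not expected to reduce recall bias in category 3.

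**The concern.** A visit made after a dose cannot change whether or when that dose was given. The outcome, however, is not observed dosing. It is a classification made at the visit from the caregiver's answers and, where there is one, the pack. How far the visitor probes, how an approximate time is rounded against a window of one or two hours, and whether a claim of correct dosing is accepted without a pack are all settled after dosing. They are settled by someone from whom the arm is not concealed.

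At stake are the first primary outcome and the secondary outcomes on individual doses. The second primary outcome, attendance for the day 3 review, does not depend on what home visitors record.

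**Working it through.** **1. Which parts of the outcome are open to the visitor's judgement**

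| Element | Physical check at the visit | Rests on the caregiver's report |
|---|---|---|
| Tablets left in a presented pack (non adherent) | Yes | No |
| Empty pack (adherent) | Yes, tablets are gone | Dose times and schedule |
| No pack (probably adherent, probably non adherent) | None | Entirely |

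A pack can show that tablets are gone, not when they were given. Timing and no-pack cases are the exposed part. The documents do not give their share of all children.

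**2. The plan's own sample size**

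Inputs (Sample size estimation): 65% against 75%, 80% power, level 0.05, 15% loss. Two-sided testing is assumed, since sidedness is not stated.

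n = [1.96·√(2·0.70·0.30) + 0.842·√(0.65·0.35 + 0.75·0.25)]² / 0.10² = 329 per arm

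329 / 0.85 = 388 (411 with continuity correction), consistent with the stated 400. Evaluable per arm: 400 × 0.85 = 340.

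**3. Illustration of differential recording**

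Assumptions:
- True adherence is 65% in both arms and the outcome is treated as adherent or not.
- A fraction f of truly non-adherent children is recorded as adherent in the SMS arm only. The documents give no such rate, so f is assumed.

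False difference: d = 0.35·f. Recorded SMS-arm proportion: p₂ = 0.65 + d.

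Rejection probability of the two-sided pooled z-test:
Φ[(d − 1.96·SE₀)/SE₁] + Φ[(−d − 1.96·SE₀)/SE₁],
where SE₀ = √(2p̄(1−p̄)/n), p̄ is the mean of the two proportions, and SE₁ = √{[0.65·0.35 + p₂(1−p₂)]/n}.

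*f = 5%, n = 340:* d = 0.0175, p₂ = 0.6675, SE₀ = 0.03636, SE₁ = 0.03636. Upper tail Φ(−1.48) = 0.070, lower tail Φ(−2.44) = 0.007, total 0.077.

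*f = 10%, n = 340:* d = 0.035, p₂ = 0.685, SE₀ = 0.03613, SE₁ = 0.03611. Upper tail Φ(−0.99) = 0.161, lower tail Φ(−2.93) = 0.002, total 0.162.

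| f | False difference | Two-sided rejection, 340 per arm |
|---|---|---|
| 0 | 0 | 5.0% |
| 5% | 1.75 points | 7.7% |
| 10% | 3.5 points | 16.2% |

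The two-sided total is the figure to set against 5%. The upper tail alone has a null value of 2.5%.

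**4. Why this is an upper illustration at a given f**

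The calculation applies f to the whole 35% who are non-adherent. Children with tablets left are fixed by a count. If, say, only half of the 35% were open to reclassification, f = 10% would give 0.35 × 0.5 × 0.10 = 1.75 points, which is the 7.7% row.

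**The case against.** The plan is frank about the lack of masking, gives a reason for it, and calls the absence of effect a belief. Leftover tablets are a physical check. Under Trial monitoring and oversight, the Data Monitoring Board is to look, in blind, at a sizeable share of the primary outcome data. The bias that the Quality control section names comes from the caregiver, which is a different mechanism from bias by the visitor. Because the trial is open label, masking visitors would leave the caregiver's own reporting bias in place.

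All of this is correct, and it limits the point without answering it. The tablet count does not reach dose times or children without a pack. Blind review takes place after the answer is on the form and cannot undo how it was obtained. The Quality control text supports only that the outcome depends on report; it is not evidence that visitors distort it.

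A reader might also infer three stronger things that the documents do not support:
- **That the bias favours SMS.** It could, but nothing in the article fixes its direction.
- **That the visit form asks about SMS first, or that visit lists or identifiers reveal the arm.** The article gives no question order and does not describe the lists. It says only that a random number serves as the unique identifier. A condensed article need not give such detail.
- **That reordering the form would solve the problem.** A caregiver asked when a dose was given may answer by mentioning the message, so ordering only reduces the risk.

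**Conclusion.** The stated reason does not carry its conclusion. Timing protects the dosing behaviour. It does not protect the eliciting and recording of reported dose times, or of claims of correct dosing made without a pack. Differential recording therefore remains possible for the first primary outcome and the dose-level outcomes. That much rests on the text alone and is firm.

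The size is not known. The range of 1.75-3.5 points, with about 8-16% two-sided rejection under no true effect, depends on an assumed 5-10% misrecording rate in one arm only, 65% true adherence in both arms, 340 evaluable per arm, and every non-adherent child being open to reclassification. The last assumption makes it an upper figure for those rates. It is an illustration of sensitivity, not an estimate, and it does not show that the trial's result would be biased. The change is worth making because it is cheap and concerns a primary outcome.

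**What to change.** 1. Give home visitors lists that carry the identifier and visit day but not the arm.
2. Have them complete the blister-pack count and dose times, and lock that part by signature or time stamp, before opening the SMS-exposure section. Put that section last and ask it of all caregivers in both arms.
3. Record for each visit whether the arm became known before locking.
4. Replace the claim under Allocation of participants to trial groups with a limitation, for example: *Home visitors may learn the allocation. Because adherence is partly reported, differential recording by arm cannot be excluded; the pack count is a partial check.*

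**Cost.** A reordered form and a short retraining, with no extra staff or visits. Some caregivers will still reveal the arm, and caregiver reporting bias is untouched. Overall study design says the randomised phase began in June 2014, so a change after that date means that adherence data come from two procedures. The date of change should then be recorded and the outcome compared before and after it. Step 4 can be done at any stage.
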